### Sample Size

Patients who have agreed to participate in the treatment study will be randomized in a 1: 1 ratio between intervention and control group. In our power calculation, we estimated that 40% in the intervention group and 20% in the control group will see improvement through the treatment offered in different groups, and after this treatment fall under the cutoff for problem gaming. With these figures, 160 (80 + 80) patients must be included in the treatment study for us to be able to demonstrate a significant difference with sufficient power. Given the large number of patients in pediatric and youth psychiatry in the region and the likely high incidence of problem behaviors in the population, we believe it is possible to reach this number of participants in the study.

### Ethics Approval

The study was reviewed and approved by the Swedish Ethical Review Authority (Ref 2019-04797, December 13, 2019). Subsequent amendments have been approved (Ref 2021-05592-01, January 3, 2021; Ref 2022-01289-02, March 15, 2022).

### Informed Consent

After eligibility is confirmed, written and verbal information about the study will be provided to all participants according to the Swedish Act concerning the Ethical Review of Research Involving Humans (SFS 2003:460). All patients, their carers, and clinicians who verbally agree to take part in the project will be provided with a consent form enabling them to provide written consent. For patients below the age of 15 years, a carer’s written consent will be needed for their children to take part in the study. All participants will be informed that their partaking in the study is voluntary; their data would be handled with strict confidentiality; results will be reported on a group level, which means that individual participants will not be identifiable; and they are free to withdraw from the study at any time without reporting a reason for withdrawal. Please see Multimedia Appendix 1 for details. The trial intervention is similar to other clinical practices offered in child and youth psychiatric clinics, which is why we consider the risks with the trial as minimal.

### Measures and Data Collection

Background information, including gender, age, housing situation, and diagnosis, as well as primary outcome measures assessing gaming and gambling problems, will be collected via the platform “Blå appen” (“Blue application” in Swedish). Blå appen is a digital platform developed by the child and youth outpatient department in Region Skåne, distributing and summarizing online self-rated questionnaires. It is used throughout Swedish child and youth psychiatry to facilitate the usage of self-rated questionnaires to patients. The secondary outcome measures, including parent-child communication and connectedness and family climate, will be administered in paper format after the child has provided consent to the study. Because the secondary outcomes measures assess general parent-child interactions, specific questions about gaming will also be added. The patients who consent to the RCT will rate their gaming and gambling activity as well as their parent-child relationships before and after the treatment. The “treatment at usual” arm will do the rating of gaming and gambling activity as well as their parent-child relationships at the inclusion and 3 months after the inclusion to the study. The following primary outcome measures will be used:

The Game Addiction Scale for Adolescents [24] applies to gaming behavior during the previous 6 months based on 7 items. Each question covers one criterion in the DSM-5, answered on a 5-point Likert scale ranging from 1 (never) to 5 (very often) and should according to the developer be counted as endorsed when rated 3 or higher.The Diagnostic Screen for Gambling Problems–Control, Lying, and Preoccupation (NODS-CLiP) [25] is the shorter form of the NODS [26], which assesses gambling problems. NODS yield a score ranging from 0 to 10, corresponding to the DSM-4 criteria for gambling, where a score of 5 or more qualifies as pathological, a score of 3-4 corresponds to the subclinical syndrome of problem gambling, and scores of 1-2 corresponds to an “at-risk” status. NODS-CLiP comprises the 3 NODS items that best describe problem gambling, with 3 NODS questions pertaining to loss of Control, Lying, and Preoccupation—the “CLiP.”

The following secondary, somewhat adapted, outcome measures will be used:

Parent-child communication [27] includes six subscales: (1) parent knowledge of child activities (eg, “Do your parents know how much time you spend on gaming?”); (2) parent control (eg, “How often do your parents set rules about your gaming activities?”); (3) parent solicitousness (eg, “How often do your parents ask you about your gaming activities?”); (4) child disclosure (eg, “Do you tell your parents about your gaming activities?”); (5) child secrecy (eg, “Do you hide a lot from your parents in terms of your gaming activities?”); and (6) child feelings of being overly controlled (eg, “Do you think your parents want to know too much about your gaming activities?”). Items are rated on a 5-point Likert scale ranging from 1 (often) to 5 (never).Family climate [28] includes 2 subscales, family cohesion and conflict. Although family cohesion assesses the bonds between family members (eg, “In my family, we help and support each other”), family conflict assesses the conflicts between family members (eg, “In my family we often fight with each other”). Items are rated on a 4-point scale, ranging from 1 (not true at all) to 4 (very true).

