### Intervention

There is at this time a lack of consensus regarding treatment methods for problem gaming [22], in part due to a lack of clinical research [23]. However, together with 4 experienced psychologists in the field, we developed a manual drawing on previous knowledge in the field of addiction and the field of child and adolescent psychiatric treatment. Relapse prevention for alcohol and substance abuse was used as a theoretical underpinning [20] to develop a manual with 2 aspects in mind: adapting the blurbs and examples for children and adolescents—in part by including a fictionalized adolescent when demonstrating the theme of the particular session; and by structuring the sessions so that they could be easily adapted to fit the participant’s primary problem behavior—gaming or gambling. Patients who meet the criteria for disordered gambling or gaming (according to tentative criteria from the DSM-5) will be offered the opportunity to participate in a relapse preventive treatment intervention at their local clinic or where applicable at an adjacent clinic. The treatment will be administered in an individual format and consist of 7 to 9 sessions of 45 minutes over a period of 7 to 9 weeks. The treatment will be offered to participants both in person and via video link to facilitate participation for children and adolescents living further away from the participating clinics.

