The treatment consists of three parts: (1) setting goals, (2) understanding and identifying high-risk situations and problem behaviors, and (3) consolidating the new activity schedule and identifying future high-risk behaviors. The first part is focused on examining the patient’s undesirable behavior, his/her motivation for change, and establishing goals with the treatment (this part primarily draws on motivational interviewing). This part of the treatment therefore varies between 1 to 3 sessions as participants may have different levels of motivation for changing their primary problem behavior, which is why some participants may require 1 or 2 extra sessions at the start of the treatment. The second part (drawing more from traditional CBT techniques) consists of exploring problematic situations using functional analysis; identifying high-risk situations and events, emotions, and cognitions that induce the problematic gaming behavior or result in a relapse; and managing game time with activity scheduling and practicing problem-solving skills. The final part consists of recognizing early warning signals that may indicate that the primary problem behavior is more likely to occur and consolidating the parts of the treatment that have been the most helpful in maintaining the new activity schedule.

Clinicians (psychiatrists and psychologists) with training in CBT will beforehand be educated in relapse prevention and will throughout the treatment be supervised by a clinician with vast experience of treating adults with gambling and gaming addictions.

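### Post ratings are timed from the end of therapy in one arm and from inclusion in the other, so elapsed time can differ systematically by arm

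*Protocol article*

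**What the plan says.** Two consecutive sentences in the protocol article, Measures and Data Collection, set the rating times. Consenting patients "will rate their gaming and gambling activity as well as their parent-child relationships before and after the treatment". The treatment-as-usual arm then gets its own timing: it rates gaming, gambling and "parent-child relationships at the inclusion and 3 months after the inclusion to the study".

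The Intervention section gives the therapy as "7 to 9 sessions of 45 minutes over a period of 7 to 9 weeks". It adds that "some participants may require 1 or 2 extra sessions at the start of the treatment", because the opening motivational part takes 1 to 3 sessions.

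The primary gaming scale "applies to gaming behavior during the previous 6 months based on 7 items". For the sample size, "we estimated that 40% in the intervention group and 20% in the control group" would improve and fall below the problem-gaming cutoff, and on that basis "160 (80 + 80) patients must be included in the treatment study".

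No section states the time from inclusion to the first session, links the relapse prevention post rating to 3 months, or sets a window common to both arms.

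**The concern.** One arm's post rating follows an event (the end of therapy) and the other's follows the calendar (3 months from inclusion). Randomisation balances the children, but not the time over which they are observed. Anything that changes with time alone can then enter the between-arm difference: spontaneous improvement, regression to the mean, school term, or how a child answers just after finishing therapy.

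All primary and secondary outcomes follow these schedules, so all between-arm comparisons are exposed. Because elapsed time largely coincides with arm, modelling afterwards cannot separate the two without assumptions that the data cannot test. An analysis plan that is not shown here could therefore soften the problem but not remove it.

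**Working it through.** **1. The plan's own figure.** The inputs are 40% against 20% and 80 per arm (Sample Size). Alpha and power are not stated; I assume 5% two-sided and 80%. With pooled variance:

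n = [1.960·√(2·0.30·0.70) + 0.842·√(0.40·0.60 + 0.20·0.80)]² / 0.20² = (1.270 + 0.532)² / 0.04 ≈ 81.2, so 82 per arm (164 in total).

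The unpooled form gives (1.960 + 0.842)²·0.40/0.04 ≈ 78.5, so 79 per arm. The stated 160 is reproduced closely, and power at 80 per arm is 79.4%. The calculation is sound. It takes the two percentages as comparable, which calls for comparable rating times.

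**2. The two intervals.** Three months is 365.25/12 × 3/7 = 13.04 weeks. Therapy lasts 7 to 9 weeks.
- If therapy starts at inclusion, the relapse prevention post rating falls 13.04 − 9 = 4.0 to 13.04 − 7 = 6.0 weeks before the control one.
- If there is a wait of L weeks, the post rating falls L + 7 to L + 9 weeks after inclusion. A wait of about 4 to 6 weeks would bring it near 3 months. A longer wait puts it after the control rating.
- If the first rating is taken just before therapy, the interval between ratings remains 7 to 9 weeks whatever the wait.

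**3. Spread within the intervention arm.** The motivational part takes 1 to 3 sessions. At about one session a week, that moves the post date by up to about two weeks, in this arm only and in relation to motivation.

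**4. Recall window.** Six months is about 26.1 weeks. The share of the window lying after the first rating is 7/26.1 = 27% to 9/26.1 = 34–35% for a 7 to 9 week interval, and 13.04/26.1 = 50% for controls.

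**5. Illustration of size.** Assumptions: therapy starts at inclusion, and the treatment-as-usual rate p at 13.04 weeks accrues at a constant hazard. Background improvement at week w is 1 − (1 − p)^(w/13.04).

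| p at 3 months | at 7 weeks | at 9 weeks | shift in points |
|---|---|---|---|
| 10% | 5.5% | 7.0% | −4.5 to −3.0 |
| 20% (plan) | 11.3% | 14.3% | −8.7 to −5.7 |
| 30% | 17.4% | 21.8% | −12.6 to −8.2 |

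A negative shift works against relapse prevention. With p = 20% and no treatment effect, the two-sided 5% test at 80 per arm would reject in about 33% of trials (7 weeks) or 16% (9 weeks), nearly always in favour of control.

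**6. Reversal.** If baseline is at inclusion and a wait puts the post rating at 17 weeks, the same formula gives 25.2% against 20%. That is a shift of +5.2 points towards relapse prevention, with rejection in about 12% of null trials.

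**The case against.** The best defence is that the article shows non-aligned anchors and no more. Several stronger statements that a reader might infer are not supported:

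- **Different baseline dates.** The text places the first relapse prevention rating before treatment, which fits a rating at inclusion. Screening takes place at the first visit for all children, and the paper questionnaires follow consent in both arms. A differing baseline is possible but not stated.
- **A known gap of 4 to 6 weeks.** The 7 to 9 weeks is the length of therapy, not the time from inclusion to the post rating. Three months may have been chosen as a stand-in for the end of therapy.
- **A rate for untreated children.** The 20% is the expected improvement under treatment as usual.
- **A measured bias of 6 to 9 points.** A constant rate is an assumption. Regression to the mean need not build up in proportion to time, and the long recall windows overlap heavily.
- **A known loss of power.** Subtracting the shift from 40% would leave 31% to 34% against 20% and power of 37% to 53%. But the 40% can be read as already the rate at the end of therapy, and the subtraction would then count timing twice.
- **No rating for children who stop early.** How they are followed up is detail that an article may leave to the full protocol.

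All of this stands as a limit on size and direction. It does not remove the core: read together, the two sentences give the arms different anchors, and nothing in the article brings them into line. The first sentence could literally cover all consenting patients, but the next gives controls a separate schedule, so two schedules is the natural reading. An early rating under the illustration would be conservative for a claim of benefit, but since the sign is open, the design cannot rely on that.

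**Conclusion.** The point holds in this form: the post rating is anchored to the end of therapy in one arm and to inclusion in the other, with no stated alignment, so the between-arm contrast on every outcome mixes treatment with elapsed time. This rests on the text alone and needs no numerical assumption.

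The size depends on what the article does not give. Under an immediate start and constant accrual, it is about 6 to 9 points against relapse prevention, with a range of 3 to 13 points for 3-month rates of 10% to 30%. That is large enough to matter beside a planned 20 points. The sign could be the opposite. The figures show plausible scale and are not estimates for this trial.

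The length of therapy is itself less certain than it looks: the Background describes the programme as 3 to 8 sessions and the Intervention section as 7 to 9. These two sections must be reconciled.

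**What to change.** Rate both arms on one schedule counted from inclusion. Take baseline in both arms at inclusion, before the allocation chit is drawn. Take the comparative post rating in both arms 3 months after inclusion, within the same window, whether or not therapy was completed. A rating at the end of therapy may remain as an extra, but should not be used for the comparison between arms.

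The cost is modest. Controls are already rated at 3 months, and 7 to 9 weeks of therapy fits within 13 weeks if it starts soon after inclusion. The main change is the post date for one arm, on the questionnaire platform and the paper forms. It needs a small amendment, possibly with ethics approval. Because recruitment began in January 2022, some children may already have been rated under the present schedule. They must be identified, actual rating dates recorded for everyone, and a sensitivity analysis run using those dates. That analysis will show how far the result depends on timing, but it cannot fully correct the ratings already taken.

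### The gaming primary scale looks back 6 months, longer than the stated follow-up, so at least half of the control post window, and about two thirds or more of the intervention window if rated at end of treatment, shows behaviour from before the trial or treatment began

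*Protocol article*

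**What the plan says.** Under Measures and Data Collection, the protocol article names the Game Addiction Scale for Adolescents as a primary outcome and says that it "applies to gaming behavior during the previous 6 months based on 7 items". Each item runs from 1 to 5 and counts as endorsed at 3 or higher.

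The Intervention section sets the treatment at "7 to 9 sessions of 45 minutes over a period of 7 to 9 weeks".

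The rating times are described separately, again under Measures and Data Collection. Consenting patients rate gaming and gambling "as well as their parent-child relationships before and after the treatment", with no calendar date. The treatment-as-usual arm rates "at the inclusion and 3 months after the inclusion to the study".

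The Sample Size section assumes that "40% in the intervention group and 20% in the control group will see improvement", and defines improvement as patients who "after this treatment fall under the cutoff for problem gaming". It concludes that "160 (80 + 80) patients must be included in the treatment study".

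Nothing in the article shortens the look-back for the post rating, adds a later rating, or mentions the overlap between the look-back and the time before treatment.

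**The concern.** A child who follows the scale's instruction at the post rating must still report on months that came before treatment, and in the control arm before inclusion. Those months also fed the baseline score. A real change can therefore show up only in part, and a child who has improved may still endorse enough items to stay above the cutoff.

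Two things are at stake. First, the powered event becomes harder to observe, so the difference between arms is likely to shrink and power with it. Second, if the intervention arm is rated sooner than controls, its window holds more of the earlier period, and the comparison tilts against the intervention. The instrument, its look-back and the rating times are all fixed in the article. No later analysis can remove the earlier months from an answer already given.

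**Working it through.** **1. The plan's own figure.** Inputs from Sample Size: 40% versus 20%, 80 per arm. The article gives neither alpha nor power as a number, so two-sided 0.05 and 80% are assumed.

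n per arm = [1.960·√(2·0.30·0.70) + 0.842·√(0.40·0.60 + 0.20·0.80)]² / 0.20² = (1.270 + 0.532)² / 0.04 ≈ 82, or 164 in total.

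With unpooled variance the result is 79 per arm, 158 in total. Power at 80 per arm is 79.4%. The stated 160 is reproduced, with no visible margin.

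**2. Share of the post window before the start.** Inputs: look-back 6 months ≈ 26 weeks; treatment 7 to 9 weeks; control rating at 3 months ≈ 13 weeks. Share = 1 − (weeks since start) / 26, where the start is the first session in the intervention arm and inclusion in the control arm.

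| Post rating | Share before the start |
|---|---|
| 7 weeks (intervention, end of treatment) | 19/26 = 73% |
| 8 weeks | 18/26 = 69% |
| 9 weeks | 17/26 = 65% |
| 13 weeks (control) | 13/26 = 50% |

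The intervention rows assume a rating at end of treatment. In those rows the other 27-35% of the window is the treatment period itself, while change is still building.

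**3. What this could do to one item (illustration).** Assume that answers average evenly over the window and that the child changes at once and fully to a 1.
- From 5: (19·5 + 7·1)/26 = 3.9 at 7 weeks; (17·5 + 9·1)/26 = 3.6 at 9 weeks; (13·5 + 13·1)/26 = 3.0 at 13 weeks. The item is still endorsed each time.
- From 4: (19·4 + 7·1)/26 = 3.2 at 7 weeks; (18·4 + 8·1)/26 = 3.1 at 8 weeks; (17·4 + 9·1)/26 = 2.96 at 9 weeks; (13·4 + 13·1)/26 = 2.5 at 13 weeks. It is endorsed at 7 and 8 weeks, but not at 9 or 13.

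Under this model a full change can go uncounted, and the same change can count at the control rating time but not at an earlier intervention rating.

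**4. What a smaller difference would do to power (illustration).** Control rate held at 20%, 80 per arm, two-sided 0.05.

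| Intervention rate | Power | Total N for 80% power |
|---|---|---|
| 40% (as planned) | 79% | 164 |
| 38% | 71% | 198 |
| 35% | 57% | 276 |
| 30% (half the difference lost) | 31% | 588 |

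If the 20-point difference shrank in proportion to the window, the intervention rate would be 20 + 20·9/26 = 26.9% at 9 weeks or 20 + 20·7/26 = 25.4% at 7 weeks, with power of 18% or 13%. The article does not say where in this range the trial would fall.

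**The case against.** The strongest reply is that much of this rests on inference.

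- **Timing.** The article gives no date for the intervention arm's post rating. The 7 to 9 weeks is the length of treatment, not a rating time. If that arm were rated about 13 weeks after its first session, the share would be 50% in both arms and the differential bias would vanish. This stands: the 65-73% and the bias between arms are conditional.
- **Recall.** Children may weight recent weeks, and a thresholded item need not shrink in proportion to the window. This stands too, and is why the item and power figures above are illustrations only.
- **Planning rates.** The 40% and 20% may already allow for the look-back. The article does not say so, but it does not exclude it.
- **Direction.** The likely error is towards no difference. It costs sensitivity and does not manufacture a benefit.

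A reader might go further and infer that most of the window is pre-treatment in both arms, that falling under the cutoff can hardly be seen at all, or that a null result would be uninterpretable. The article supports none of these. Three months of six is exactly half. The event is harder to observe, not unobservable. A null result would be harder to read, but not empty.

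What the reply does not remove is the control arm, where the article fixes both the look-back and the rating time. The look-back there is twice the follow-up.

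**Conclusion.** The concern holds. Under the stated schedule, half of the control post window precedes inclusion. If the intervention arm is rated at end of treatment, 65-73% of its window precedes treatment. Attenuation of the effect on the powered event is probable. A bias against the intervention is added if that arm is rated earlier than controls.

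The size cannot be computed from the article. It depends on how children use the look-back, on the actual rating date, and on whether the planning rates already allow for the window. The stated 160 gives about 79% power at the assumed alpha, so even a modest loss matters: a fall from 40% to 35% in the intervention arm would take power to 57%.

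**What to change.** Keep the 6-month wording, and keep the existing ratings as short-term outcomes. Add one self-rating through the existing app, at the same fixed time from inclusion in both arms, late enough that the whole 6-month window lies after the scheduled end of treatment. That is 9 + 26 = 35 weeks or more from inclusion, plus any delay to the first session. Base the primary cutoff comparison on this rating.

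**Feasibility.** Recruitment ends on 30 December 2022 (Design). Adding 35 weeks gives about 1 September 2023, which leaves 13 weeks before 1 December 2023 for delayed starts; the trial is stated to end in December 2023 (Results).

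**Costs.**
- Some extra non-response. If 10% were missing in each arm (an assumption), 72 per arm would remain, and power at 40% versus 20% would be Φ[(0.20·√72 − 1.270)/0.632] ≈ 75%.
- The primary result would describe a sustained effect rather than an end-of-treatment effect, which is a different question and should be stated as such.
- The first results expected in March 2023 could not include this rating for later recruits.

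Shortening the look-back for the outcome ratings is a weaker alternative. It departs from the scale's stated recall period, leaves the cutoff without support under the new wording, and does not match baselines collected since January 2022.

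At minimum, rate both arms at the same time from inclusion, give that date, and state the attenuation expected and whether the 40% and 20% already allow for it.
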